#### Secondary outcomes

Secondary outcomes include symptoms that have been found to be of special relevance in Long COVID, such as fatigue,^31^ post-exertional malaise^32^ and pain.^33^ We will also include a self-developed screening questionnaire on Long COVID as well as other post-infectious symptoms. This self-report instrument, called the PHQ-15 Post-Acute Infection Syndromes (PHQ-15 PAIS), is based on the PHQ-15^25^ and extended for the most common symptoms in post-acute infection syndromes.^34^ Illness-related anxiety (Somatic Symptom Disorder – B Criteria Scale (SSD-12)),^35^ expectations of symptom severity, burden, treatment outcome and coping with symptoms (Treatment Expectation Questionnaire (TEX-Q); European Research Network to Improve Diagnosis, Treatment and Health Care for Patients with Persistent Somatic Symptoms (EURONET-SOMA) numeric rating scales)^36,37^ will be investigated as pre-specified mediator variables. The treatments received will be documented. In addition to Long COVID-specific outcome variables, we will apply the joint core measures of the SOMACROSS Research Unit to identify further risk factors and mechanisms for symptom persistence in Long COVID, and to make the results of the studies comparable. The joint core set of instruments is described in detail in the overarching protocol of the SOMACROSS Research Unit.^12^ Supplements from the core set include, for example, adverse childhood experiences, negative affectivity, stigmatisation, health-related quality of life and healthcare utilisation. As in the research unit, we will also conduct the Structured Clinical Interview for the DSM-5 (SCID-5) for the diagnosis of somatic symptom disorder according to the DSM-5, to investigate the diagnosis as a potential predictor of treatment response.

#### Safety outcomes

To the best of our knowledge, there is no risk for serious adverse events caused by the application of expectation management interventions.^27^ However, patients may develop severe somatic complications of Long COVID or other medical conditions. In these cases, patients will be informed and advised to initiate appropriate treatment. In case of an emergency, medical treatment will be initiated at the University Medical Center Hamburg-Eppendorf. Any adverse events will be systematically recorded at each follow-up assessment.

#### Sample size

This trial is powered with regard to the difference between intervention 1 (COV.EXPECT + TAU) and the control condition (TAU), as this is the main interest. Because of the closed testing principle, the type one error (alpha) does not need to be adjusted for multiplicity. As there are no comparable trials on Long COVID available, we based our estimation both on our DEPSCREEN-INFO trial (Increasing the Efficiency of Depression-Screening using Patient-Targeted Feedback),^38^ which yielded a between-group effect size of *d* = 0.33 in PHQ-15 scores with an intervention of much lower intensity (written feedback after depression screening), and on the PSY-HEART trial,^27^ which yielded a medium between-group effect size of *d* = 0.71 with an expectation management intervention, but using a different outcome instrument (modified version of the Pain Disability Index). Based on these two studies, we expect a medium effect size (*d* = 0.50) that can be detected with a power of 80%, using a two-sided alpha of 5%, by including 64 patients in each group, resulting in a total sample size of *N* = 192. Based on the results of our previous studies, we assume a loss to follow-up between baseline and the primary outcome measurement (i.e. 3-month follow-up) of 25%, resulting in a total of 258 randomised patients. Assuming that 50% of patients will meet the inclusion criteria, a total of 516 patients will be assessed for eligibility. Figure 2 shows the anticipated flow of participants throughout the trial.

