**Method:**

We will conduct an observer-blinded, three-arm, randomised controlled trial. A total of 258 patients with Long COVID will be randomised into three groups of equal size: targeted expectation management in addition to treatment as usual (TAU), non-specific supportive treatment plus TAU, or TAU only. Both active intervention groups will comprise three individual online video consultation sessions and a booster session after 3 months. The primary outcome is baseline to post-interventional change in overall somatic symptom severity.

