#### Statistical methods

The primary analysis and all prespecified secondary analyses will be conducted in the intention-to-treat sample consisting of all randomised patients with the full analysis set, which is as close as possible to the intention-to-treat population. In secondary analyses, the data of the per-protocol population (subgroup of patients without major protocol violations) will be used and multiple imputation will be applied.

For objective 1, a linear mixed-effects model with the change from baseline for all measured time points will be used to investigate the group differences in the PHQ-15, with treatment group, time and gender as fixed effects, patient as the random effect and baseline PHQ-15 score as the covariate. The interaction between time and treatment group will be tested and excluded from the model if *P* ≥ 0.05. For primary hypothesis, the global treatment effect after 3 months will be considered first. If the two-sided *P*-value is <0.05, the contrasts in change after 3 months for COV.EXPECT versus TAU, COV.SUPPORT versus TAU and COV.EXPECT versus COV.SUPPORT at the 5% level (two-sided hypothesis) will be considered. Because of the closed testing principle, an adjustment of the contrast *P*-values for multiplicity is not necessary.

Secondary end points will be analysed analogously to the primary end point, with the regression model corresponding to the measurement scale (mixed linear model for metric outcomes, mixed logistic model for binary outcomes, cumulative logit model for ordinal outcomes).

In subsidiary analyses, a potential effect of recruitment settings will be investigated by including the setting as a further fixed effect in the analysis. To analyse whether treatment effects on Long COVID resulted through changes in illness-related anxiety or symptom expectations, we will conduct mediation analyses.

To identify further risk factors involved in the persistence of Long COVID (objective 2), we will use longitudinal data from the control group and conduct multivariate regression analyses with symptom persistence as outcome, taking into account the number of predictors and sample size. Patients from the intervention groups will not be included in these analyses because the interventions could bias the results.

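### The stated 80% power belongs to COV.EXPECT versus TAU tested alone; with the global test that must be passed first, the same calculation gives about 70–76%

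*Protocol article*

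**What the plan says.** In the protocol article, the section Sample size names one contrast as the basis for the calculation: "This trial is powered with regard to the difference between intervention 1 (COV.EXPECT + TAU) and the control condition (TAU"). It then gives the assumption, "we expect a medium effect size (*d* = 0.50"), and the result, "that can be detected with a power of 80%, using a two-sided alpha of 5%, by including 64 patients in each group". Over three arms this makes 192 analysed patients. Allowing for loss to follow-up at the primary time point ("i.e. 3-month follow-up) of 25%, resulting in a total of 258 randomised patients"), the total becomes 258, allocated equally to three arms ("will be randomised into three groups of equal size"). On multiplicity it says: "Because of the closed testing principle, the type one error (alpha) does not need to be adjusted for multiplicity".

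The section Statistical methods sets the order of testing: "For primary hypothesis, the global treatment effect after 3 months will be considered first". Only if its two-sided P-value is below 0.05 are the three pairwise contrasts examined, each at two-sided 5%. The model is a linear mixed model for change in PHQ-15 at all measured time points, with baseline PHQ-15 as covariate.

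The article states no effect for COV.SUPPORT, no power for the global test or for the two steps together, and no baseline–outcome correlation.

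**The concern.** The two sections describe different procedures. The power figure is for one contrast tested directly at 5%. The analysis requires two rejections before that contrast can be declared: the global test and then the contrast. The probability of both cannot exceed the probability of the contrast alone, and it also depends on where the COV.SUPPORT mean lies.

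Closed testing is correctly cited for the type I error. With three arms, a significant global test followed by unadjusted contrasts controls the family-wise error. But that says nothing about power, and the sample size text moves from one to the other without counting the cost.

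At stake is the chance of missing the assumed effect on the contrast the trial was sized for: about 24–30% on the sample size section's own scale, against the 20% stated.

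**Working it through.** **Inputs from the article.** d = 0.50 (SD = 1), 64 analysed per group, three equal groups, two-sided 5%, global test first, 25% loss.

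**Assumed input.** The COV.SUPPORT effect versus TAU, s, is varied from 0 (equal to TAU) to 0.5 (equal to COV.EXPECT).

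**1. Reproduce the stated figure.** Noncentrality = 0.50 × √(64/2) = 2.83. With 126 df, two-sided 5%, power is 80.1%. With the variance pooled over three arms (189 df) it is 80.3%. Dropout: 64/0.75 = 85.3, rounded up to 86; 3 × 86 = 258. Both figures reproduce, and the global test plays no part in them.

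**2. What the global test adds.** With equal groups, 2F = t² + u². Here t is the COV.EXPECT versus TAU statistic and u is the statistic for COV.SUPPORT against the mean of the other two arms. The contrast alone needs |t| > 1.973, that is t² > 3.89. The global test needs F(2, 189) > 3.044, that is t² + u² > 6.09. If COV.SUPPORT lies midway, u is centred on zero and gives little help, so the global test is the harder hurdle.

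**3. Power of the global test alone.** λ = 64 × Σ(μ − mean)².
- Means 0 / 0 / 0.5 (or 0 / 0.5 / 0.5): Σ = 0.1667, λ = 10.67, power 83.5%.
- Means 0 / 0.25 / 0.5: Σ = 0.125, λ = 8.0, power 71.0%.

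**4. Power of both steps together** (simulation, 1,000,000 draws per scenario, pooled variance):

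| COV.SUPPORT vs TAU (SD) | Global test | Contrast alone | Both |
|---|---|---|---|
| 0 | 83.5% | 80.3% | 76.0% |
| 0.1 | 76.2% | 80.3% | 72.7% |
| 0.2 | 71.6% | 80.3% | 70.3% |
| 0.25 | 71.0% | 80.3% | 69.8% |
| 0.3 | 71.6% | 80.3% | 70.2% |
| 0.4 | 76.2% | 80.3% | 72.7% |
| 0.5 | 83.5% | 80.3% | 76.0% |

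Just outside the range (s = −0.1 or 0.6) the joint power is about 78.6%. The dropout allowance holds no reserve: 258 × 0.75 = 193.5, or 64.5 per group, which still gives 70–76%.

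**5. Size needed to keep this procedure at 80%.** About 70 analysed per group (3 × 94 = 282 randomised) if COV.SUPPORT equals either other arm; about 80 (3 × 107 = 321 randomised) at the midpoint.

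**6. Baseline adjustment.** If d = 0.50 is on the unadjusted scale and r is the baseline–outcome correlation, the effect in the analysis is 0.50/√(1 − r²).
- r = 0.30: 0.524, joint power 80% at either end.
- r = 0.45: 0.560, joint power 80% at the midpoint.
- r = 0.50: 0.577, contrast alone 90%, joint power 83–88%.

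**The case against.** The strongest reply is that the planned analysis is not the t-test used for sizing. The mixed model adjusts for baseline PHQ-15 and uses every time point, including 6-week data from patients lost by month 3, whom the sample size section treats as contributing nothing. If d = 0.50 is on the unadjusted scale, a moderate baseline correlation brings the two-step procedure back to 80% or more. This stands. A reader might infer from the table that the trial is underpowered; the document does not support that, because it fixes neither the scale of d nor the correlation. It is equally true that the sample size section claims no such gain, and that with r = 0.5 requiring the global test still costs 2–7 points against the contrast alone.

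Second, the 70% end is not a consequence of the plan's inputs alone. It needs COV.SUPPORT at about 0.2–0.3 SD; at either end the cost is about 4 points. This also stands, so the result has to be given as a range. An intermediate effect is not far-fetched, since the article describes COV.SUPPORT as sharing the non-specific elements of COV.EXPECT without its specific ones.

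Third, starting with a global test is a legitimate choice, and 4–10 points is small beside the uncertainty in d. The two source trials gave 0.33 and 0.71, at which the contrast alone has 46% and 98% power. That is fair as to weight. It does not make 80% the power of the procedure described.

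**Conclusion.** The 80% is right for COV.EXPECT versus TAU tested alone and wrong for the two-step procedure in the same article. On the sample size section's own scale, the procedure has about 76% power if COV.SUPPORT equals TAU or COV.EXPECT and about 70% if it lies midway, a loss of roughly 4 to 10 points. This rests on d = 0.50 being the standardised effect in the analysis, on 64 analysed per group, and on an assumed COV.SUPPORT effect between 0 and 0.5 SD.

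Two stronger readings do not hold. The closed-testing statement is not an error: no alpha adjustment is needed. Nor is a shortfall in the real trial established, since covariate adjustment may offset it. Because the power figure and the order of testing are both fixed in the article, an unseen analysis plan cannot reconcile them without changing one or stating an additional assumption.

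**What to change.** Either of two changes is enough.

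**Restate the power.** In Sample size, say that 80% applies to the contrast alone and give the power of the two-step procedure, about 70–76%, with the assumed COV.SUPPORT effect. If baseline adjustment is to be credited, state the correlation and its source. This costs a few sentences.

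**Or change the order of testing before unblinding.** Test COV.EXPECT versus TAU first at two-sided 5%. Only if it is significant, test COV.EXPECT versus COV.SUPPORT and COV.SUPPORT versus TAU, each at unadjusted 5%. If COV.EXPECT and TAU truly differ, at most one of the other two null hypotheses can be true; if they do not differ, any false claim of a difference must first pass the 5% test of the first contrast. The family-wise error is therefore controlled. The stated 80% is restored with the same 258 patients.

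The price of the second option is that the other two contrasts are tested only if the main one succeeds, with a power loss of at most about 7 points over the assumed range: COV.SUPPORT versus TAU at 0.5 SD falls from 76% to 69%, and at 0.25 SD from 28% to 27%. The change must also be listed in the registry and publications, as the section Ethical approval requires.

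A strict three-step sequence with COV.SUPPORT versus TAU last should be avoided. It would cut the chance of confirming that contrast to about 2–3%, although the design rationale asks whether both interventions improve on TAU.

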**Fig. 2 fig02:**
[figure not shown]
Anticipated flow of participants through the course of the study. Outcomes after 6 months are secondary and were not included in the sample size estimation. COV.EXPECT, expectation management intervention; COV.SUPPORT, supportive intervention.

#### Statistical methods

The primary analysis and all prespecified secondary analyses will be conducted in the intention-to-treat sample consisting of all randomised patients with the full analysis set, which is as close as possible to the intention-to-treat population. In secondary analyses, the data of the per-protocol population (subgroup of patients without major protocol violations) will be used and multiple imputation will be applied.

For objective 1, a linear mixed-effects model with the change from baseline for all measured time points will be used to investigate the group differences in the PHQ-15, with treatment group, time and gender as fixed effects, patient as the random effect and baseline PHQ-15 score as the covariate. The interaction between time and treatment group will be tested and excluded from the model if *P* ≥ 0.05. For primary hypothesis, the global treatment effect after 3 months will be considered first. If the two-sided *P*-value is <0.05, the contrasts in change after 3 months for COV.EXPECT versus TAU, COV.SUPPORT versus TAU and COV.EXPECT versus COV.SUPPORT at the 5% level (two-sided hypothesis) will be considered. Because of the closed testing principle, an adjustment of the contrast *P*-values for multiplicity is not necessary.

Secondary end points will be analysed analogously to the primary end point, with the regression model corresponding to the measurement scale (mixed linear model for metric outcomes, mixed logistic model for binary outcomes, cumulative logit model for ordinal outcomes).

In subsidiary analyses, a potential effect of recruitment settings will be investigated by including the setting as a further fixed effect in the analysis. To analyse whether treatment effects on Long COVID resulted through changes in illness-related anxiety or symptom expectations, we will conduct mediation analyses.

To identify further risk factors involved in the persistence of Long COVID (objective 2), we will use longitudinal data from the control group and conduct multivariate regression analyses with symptom persistence as outcome, taking into account the number of predictors and sample size. Patients from the intervention groups will not be included in these analyses because the interventions could bias the results.

To compare risk factors and mechanisms of somatic symptom persistence in Long COVID exploratively with those identified in the other conditions investigated in the SOMACROSS Research Unit (objective 3), we will compare the results of the disease-specific regression analyses from the SOMACROSS Research Unit with the derived model from objective 2, and conduct further exploratory analyses.

Subgroup analyses will be conducted on differences in the primary outcome with respect to the following variables of interest: age, gender, education level, social support, duration and severity of Long COVID, any chronic physical disease, any mental health comorbidity, depression and anxiety. For safety analyses, adverse events will be compared between groups and analysed descriptively. Further details of statistical analyses will be described in detail in a statistical analysis plan, which will be finalised before breaking the treatment blind.

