## General aetiological model for PSS

Since there is no generally accepted disease-specific model for the development of Long COVID, we draw on disease-overarching models for the development of PSS by analogy. Regarding the transition from short-term to persistent disabling symptoms in general, the comprehensive vulnerability-stress model by Henningsen et al^13^ defines predisposing, triggering and maintaining/aggravating factors that determine the transition from short-term symptoms to PSS. Based on this model and current research findings, the German Research Foundation (DFG)-funded interdisciplinary SOMACROSS Research Unit (Persistent Somatic Symptoms Across Diseases: From Risk Factors to Modification; unit identifier RU 5211), which investigates generic and disease-specific risk factors and mechanisms for the development and maintenance of PSS across ten medical conditions, developed a cross-disease working model for the aetiology of PSS. The model is described in detail in the published framework and overarching protocol of the research unit.^9^ In brief, according to this model, predisposing factors for PSS comprise sociodemographic (e.g. female gender, poor education), psychological (e.g. precedent life stressors, negative affectivity) and biomedical risk factors (e.g. prior medical conditions, immunological predispositions). Triggering factors for short-term somatic symptoms include acute infections, injuries or current life stressors. Among the best-established maintaining/aggravating factors for PSS is illness-related anxiety,^14^ which may be explained by its association with other cognitive–perceptual and emotional mechanisms (e.g. catastrophising, somatosensory amplification) and with behavioural processes (e.g. avoidance behaviour). Besides disease-specific (e.g. inflammation, organ damage) and overarching (e.g. treatment effects) biomedical factors, dysfunctional symptom expectations are considered highly relevant for symptom persistence.^9^ Symptom expectations are defined as conscious, future-directed cognitions regarding the anticipated course of symptoms.^15^ As they constitute a common denominator of many psychological risk factors for PSS, expectations are regarded as a core feature of current aetiological models for PSS.^16^ They are also prominently conceptualised in new predictive processing models suggesting that symptom perception emerges through an unconscious, integrative process of sensory input, contextual cues and prior information. In these models, next to previous experiences, learning processes, context and prior knowledge, expectations are considered one form of prior information that contribute to the development of implicit predictions about the presence of symptoms.^17^

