## Anxiety as a risk factor for Long COVID

In a retrospective electronic health record study including 236 379 individuals, Taquet et al^2^ examined neurologic and psychiatric symptoms within the first 6 months after COVID-19 diagnosis. The highest incidence was found for anxiety disorders at 17.4%, of whom 10% had already been diagnosed before their SARS-CoV-2 infection. A recently published cohort study of 3193 individuals found anxiety and worry about COVID-19, as well as depression, perceived stress and loneliness, to be prospectively associated with an increased risk of self-reported Long COVID.^3^ Further supporting the assumption that illness-related anxiety is involved in the development and maintenance of Long COVID, we found anxiety to be the strongest modifiable predictor of somatic symptom burden after 8 weeks in a prospective cohort study of 1185 healthcare professionals that did not contract COVID-19.^4^ In the UK general population, COVID-19-related anxiety has also been found to predict somatic symptoms, particularly fatigue.^21^ Consistent with these findings, illness-related anxiety has been found to be a risk factor for PSS before the COVID-19 pandemic in a range of medical conditions, e.g. chronic fatigue, fibromyalgia and irritable bowel syndrome.^14^

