### Assessment and study outcomes

#### Measurement points

Assessments are carried out at baseline and after 6 weeks (intermediate), 3 months (post-interventional) and 6 months (follow-up). The intermediate assessment after 6 weeks is necessary for mediator analyses that investigate whether a change in symptom severity is mediated via changes in illness-related anxiety and dysfunctional symptom expectations. Except for an additional 12-month follow-up in the SOMACROSS Research Unit, assessment times are identical, allowing for comparison of results. Primary and secondary outcomes and mediator variables will be collected through electronic data entry by patients at home; only the diagnostic interview will be collected via telephone interview. The primary and secondary outcome variables and mediator variables will be measured at each assessment point, and are displayed in Table 1.

**Table 1 tab01:** Outcome instruments of the SOMA.COV study

Outcome variables (assessed via self-report/diagnostic interview)						
Predisposing, triggering and maintaining/aggravating factors	Single constructs	Instrument	Assessment time			
			0 months	6 weeks	3 months	6 months
Primary outcome: somatic symptoms	Overall somatic symptom severity	Patient Health Questionnaire-15 (PHQ-15)	X	X	X	X
Secondary outcomes: symptom-related disability	SARS-CoV-2 infection and Long COVID	Single items	X	X	X	X
	Long COVID symptoms	Patient Health Questionnaire-15 Post-Acute Infection Syndromes (PHQ-15 PAIS)	X	X	X	X
	Fatigue	Fatigue Scale (FS)	X	X	X	X
	Post-exertional malaise	DePaul Symptom Questionnaire Post-Exertional Malaise (DSQ-PEM)	X	X	X	X
	Pain	Pain Disability Index – adapted (PDI)	X	X	X	X
	SOMACROSS core measures^9^	Self-report instruments	X	X	X	X
Diagnosis of somatic symptom disorder (DSM-5)	Diagnostic classification	Structured Clinical Interview for the DSM-5 (SCID-5)	X		X	

Prespecified mediator variables (assessed via self-report)						

Cognitive–perceptual and emotional mechanisms	Illness-related anxiety	Somatic Symptom Disorder – B Criteria Scale (SSD-12)	X	X	X	X
	Treatment expectations	Treatment Expectation Questionnaire (TEX-Q)	X	X	X	X
	Expectation of symptom severity	Numeric Rating Scale (NRS)	X	X	X	X
	Expectation of symptom burden	Numeric Rating Scale (NRS)	X	X	X	X
	Expectation of coping with symptoms	Numeric Rating Scale (NRS)	X	X	X	X

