A challenge in the conduction of the study could be that some patients might be reluctant to consider psychological factors in the pathophysiology of Long COVID, which could potentially result in a lower participation rate or a higher drop-out rate than expected. To counteract this issue, we will collaborate with patient associations and self-help organisations to jointly establish communication strategies. We will also involve affected patients in the development of our expectation management intervention, an aspect that we will include in our study materials (e.g. leaflets). During the intervention, multiple mechanisms in the emergence of Long COVID will be addressed in a sensitive manner, outlining psychological variables as being one of several relevant factors for the development of Long COVID. To enhance comprehensibility, illustrative examples of everyday life will be used carefully in the conveyance of a biopsychosocial model. Finally, as part of screening interviews, potential participants will receive conclusive information about the study before inclusion to prevent drop-outs.

Considering the scientific evidence, the clinical relevance of Long COVID and the high level of suffering of affected patients, the attempt to investigate whether a targeted modification of illness-related anxiety and dysfunctional symptom expectations has a beneficial effect on Long COVID symptoms seems to be a valuable endeavour. Evidence of an effect of modifying illness-related anxiety and dysfunctional symptom expectations on Long COVID symptoms would identify an important mechanism of action, as well as be a promising starting point for future treatments for Long COVID.

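### The primary model leaves out baseline anxiety and symptom expectations, which the protocol treats as leading predictors and already measures; adding them is a modest, nearly free gain

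*Protocol article*

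**What the plan says.** The protocol article (Statistical methods) specifies a linear mixed model for change in PHQ-15 at all measured time points, "with treatment group, time and gender as fixed effects, patient as the random effect and baseline PHQ-15 score as the covariate". Anxiety and expectations do not appear in it. Table 1 (Measurement points) lists SSD-12, TEX-Q and three expectation rating scales as mediators, all marked at 0 months, 6 weeks, 3 months and 6 months. In the analysis plan they serve the mediation analyses, and anxiety is also named as a subgroup variable.

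On prognosis, the section on the general aetiological model states: "Among the best-established maintaining/aggravating factors for PSS is illness-related anxiety". It also rates dysfunctional expectations as highly relevant for persistence. The section on anxiety reports: "we found anxiety to be the strongest modifiable predictor of somatic symptom burden after 8 weeks". That cohort consisted of healthcare professionals who had not contracted COVID-19. The section on expectations reports that COVID-related symptom expectations predicted somatic deterioration 21 months later. Research needs describes both factors as apparently contributing independently of initial disease severity.

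On missing data, Sample size plans for 25% loss by 3 months. The Discussion adds that "some patients might be reluctant to consider psychological factors in the pathophysiology of Long COVID, which could potentially result in a lower participation rate", and it names attrition above the planned level as the other possible result. It lists countermeasures, among them that "potential participants will receive conclusive information about the study before inclusion to prevent drop-outs". Multiple imputation is planned as a secondary analysis. Further detail is left to a statistical analysis plan that is not shown.

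**The concern.** The covariate set is stated in full, so an analysis plan that follows the article has no room to add a primary covariate. On the authors' own theory, that set omits the two baseline constructs most likely to predict the 3-month score beyond baseline PHQ-15.

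Two things are at stake. The first is precision: a prognostic covariate reduces residual variance whether or not anyone drops out. The second is missing data. A mixed model fitted by likelihood is valid when missingness depends only on what the model contains. If loss depends on baseline anxiety or expectations, those values predict outcome, and the dependence differs between COV.EXPECT and TAU, then the retained groups are no longer comparable given the model. Some difference by arm is plausible, because TAU patients attend no sessions.

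That these scales are the planned mediators is no reason to leave them out. Mediation concerns change after baseline, and adjusting for a value taken before allocation does not block the treatment effect.

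**Working it through.** **1. The plan's own figure.** Inputs from Sample size: d = 0.50, two-sided alpha 0.05, power 80%, 25% loss. A two-sample t-test needs 63.8, so 64 per arm (power 0.801). Then 3 × 64 = 192. Inflated for loss, 64 / 0.75 = 85.3, so 86 per arm, and 3 × 86 = 258. The stated figures reproduce.

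**2. Precision.** Let R² be the share of residual variance that the added covariates explain beyond the planned model. It is not in the documents; 2–10% is assumed. The effect in residual SD units becomes d / √(1 − R²), with n = 64 per arm. The equivalent sample size is 64 / (1 − R²).

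| R² (assumed) | effective d | power | equivalent n per arm |
|---|---|---|---|
| 0 | 0.500 | 80.1% | 64 |
| 0.02 | 0.505 | 80.9% | 65.3 |
| 0.05 | 0.513 | 82.1% | 67.4 |
| 0.10 | 0.527 | 84.1% | 71.1 |

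These are powers for the single COV.EXPECT versus TAU contrast and ignore the preceding global test.

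**3. When the omission causes bias.** With partial effect b of the baseline measure A on outcome, the bias in the contrast is roughly b × (mean of A among retained COV.EXPECT patients − mean of A among retained TAU patients). It is zero if b = 0 or if retention depends on A equally in both arms.

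**4. Size in a complete-case simulation.** Assumptions: 86 per arm; 25% lost before 6 weeks in each arm; loss related to baseline expectation in COV.EXPECT only; correlation of expectation with baseline PHQ-15 of 0.4; 3-month score regressed on baseline in observed patients; 4,000 replicates. Negative values favour COV.EXPECT.

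| b (SD) | OR per SD | bias without covariate | bias with covariate |
|---|---|---|---|
| 0.2 | 1.65 | −0.022 | −0.001 |
| 0.2 | 2.7 | −0.035 | 0.001 |
| 0.2 | 4.5 | −0.044 | 0.003 |
| 0.3 | 1.65 | −0.032 | 0.000 |
| 0.3 | 2.7 | −0.055 | 0.001 |
| 0.3 | 4.5 | −0.073 | −0.002 |

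At b = 0.1 the bias is about 0.01–0.02 SD.

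**5. Size under a model closer to the planned one.** This is a random-intercept model for change at 6 weeks and 3 months, with 150,000 per arm, true effect −0.50 and Monte Carlo error about 0.005–0.01. The residual association of driver and outcome is 0.3 in every row shown.

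| scenario (loss COV.EXPECT / TAU) | without | with |
|---|---|---|
| same driver in both arms, OR 2, 25/25% | 0.001 | 0.001 |
| driver in COV.EXPECT only, OR 2, 25/25% | −0.041 | 0.001 |
| same, 6-week score observed | −0.019 | −0.003 |
| driver in COV.EXPECT only, OR 2, 35/15% | −0.058 | −0.002 |
| same, OR 3 | −0.080 | −0.002 |
| same, OR 3, 6-week score observed | −0.029 | 0.002 |
| OR 2, 35/15%, true driver correlates 0.3 with the covariate | −0.062 | −0.056 |
| OR 2, 35/15%, true driver uncorrelated with the covariate | −0.055 | −0.055 |
| same driver in both arms, 25/25%, driver also modifies the effect | −0.019 | −0.020 |

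**6. Consequence for the test.** SE = √(2/64) = 0.177. A bias of 0.02 is 0.11 SE and moves two-sided type I error from 5% to 5.1%. A bias of 0.07 is 0.40 SE and gives 6.8%. A bias of 0.08 gives 7.4%.

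**The case against.** The strongest reply is that stratification factor plus baseline outcome is a standard, prespecified covariate set, and nothing in it is wrong. That stands: this is an improvement, not a correction. Imputation detail is also fairly left to the analysis plan, so the absence of an imputation model here is not a finding.

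A reader might infer something stronger: that the protocol expects patients who resist psychological explanations to drop out, and that the omitted covariates let this drop-out bias the result towards COV.EXPECT. The documents do not support that, for five reasons.

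- The Discussion speaks only of what might happen, mentions lower participation first (which precedes randomisation), and lists countermeasures. Methods against bias adds repeated contact attempts and alternative ways of collecting data.
- Reluctance towards psychological explanations is not what SSD-12 or the expectation scales measure. With a correlation of 0.3 or 0 between the two, adjustment leaves almost all the bias in place.
- Nothing links reluctance to worse prognosis, so the direction of any bias is assumed.
- The planned model uses all time points. Where the 6-week score is observed, it already absorbs part of the problem.
- Leaving the sessions is not the same as losing outcome data when outcomes are electronic questionnaires completed at home.

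The anxiety cohort is also weaker support than its quoted result suggests, since its participants had not had COVID-19. It does not show prediction beyond baseline PHQ-15.

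**Conclusion.** The point holds as a modest improvement. The primary model omits two baseline constructs that the protocol's own rationale treats as leading predictors and that are already being collected. Adding them gains about 1–4 percentage points of power, if they explain a further 2–10% of residual variance. It also makes missing at random more plausible with a quarter of patients expected to be lost.

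Any protection against bias is conditional. It amounts to roughly 0.01–0.07 SD against a planned 0.50 (0.08 in the most extreme scenario run), and only where loss depends on these very measures and differs by arm. It is nil where the same drop-out process acts in both arms without effect modification, because no bias then arises. It is small where the driver is an unmeasured attitude. The partial effects, odds ratios and R² values are all assumptions; the documents supply only d, alpha, power, n and the 25% loss.

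**What to change.** Before unblinding, add baseline SSD-12 and the baseline expectation-of-symptom-severity rating as fixed covariates in the primary PHQ-15 model, using values recorded before allocation. TEX-Q could be a third if it is completed before allocation. Use the same variables in the planned multiple imputation. Because reluctance towards psychological explanations may be unmeasured, an arm-specific missing-not-at-random sensitivity analysis would be a sensible companion, for the analysis plan to specify.

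The cost is one sentence and two or three degrees of freedom. There is no new data collection and no change to the 258 randomised patients.
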